#### External validation

External validation will be conducted using temporal validation with data collected from September 2022 to December 2022, to ensure model portability and generalizability. This means that model risk scores will be calculated rigorously and the model will be refitted in the validation cohort.

After the model is defined, we will consider the nomogram as the final presentation form in order to facilitate clinical application of the model and assist medical personnel in identifying high-risk groups of depression in adolescents with PCOS.

All statistical analysis will be performed using R software (Windows version 4.1.2).

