**Methods and analysis:**

Model development and validation will be conducted using a retrospective study. The study will involve normal adolescent girls as the control group and adolescent PCOS patients as the experimental group. We will collect not only general factors such as individual susceptibility factors, biological factors, and psychosocial environmental factors of depression in adolescence, but will also examine the pathological factors, illness perception factors, diagnosis and treatment factors, and symptom-related factors of PCOS, as well as the outcome of depression. LASSO will be used to fit a multivariate warning model of depression risk. Data collected between January 2022 and August 2022 will be used to develop and validate the model internally, and data collected between September 2022 and December 2022 will be used for external validation. We will use the C-statistic to measure the model's discrimination, the calibration plot to measure the model's risk prediction ability for depression, and the nomogram to visualize the model.

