
## Objectives

The aims of the study are to: (i) Develop a depression prediction model for adolescents with PCOS to identify at-risk populations early; (ii) Validate the accuracy and validity of the model and to assess the clinical utility of the model.

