### Patient recruitment

Adolescents with PCOS who attend the gynecology clinic of the Affiliated Hospital of Zunyi Medical University from January 2022 to August 2022 will be selected as the potential participants using a consecutive enrollment method. The final participants will be identified based on inclusion and exclusion criteria, and data are collected as both a training dataset and a validation dataset for the model construction. Data collected from September 2022 to December 2022 as an external validation cohort. Participants listed above will comprise the experimental group. Additionally, a control group will be recruited from the gynecology clinic among healthy, age-matched adolescent girls.

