### Sample size and calculation

In the case of a binary outcome, an approximate 95% confidence interval for the total outcome proportion (ϕ) is

$$\begin{array}{l} \hat{\phi }\pm 1.96\sqrt{\frac{\hat{\phi }\left(1-\hat{\phi }\right)}{n}}, \end{array}$$

Therefore, the absolute margin of error (δ) is $1.96\sqrt{\frac{\hat{\phi }\left(1-\hat{\phi }\right)}{n}}$

For this reason, in order to get an accurate estimate of the overall outcome probability in the target population, based on the expected outcome proportion ($\hat{\phi }$) and the desired margin of error, the required sample size is calculated as: $n={\left(\frac{1.96}{\delta }\right)}^{2}\hat{\phi }\left(1-\hat{\phi }\right)$.

In general, we advise aiming for a margin of error of <0.05. Then assuming an anticipated outcome proportion in the study population of 0.4, then a minimum of 369 participants is needed to aim for an estimation error of no more than 0.05 around the actual value of 0.4 (51).

The study will include all adolescents with PCOS who attend the gynecology clinic of the Affiliated Hospital of Zunyi Medical University between January 2022 and December 2022, with an estimated sample size of 800. This study will recruit 400 healthy adolescent girls as the control group.

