#### Model-building procedures (including predictor selection)

After the data set is imported into the R software, it will be divided into 80% training data and 20% validation data. The training data will be used to build the warning model, and the validation data will be used for internal validation.

To begin with, we will use R software to read the features of the dataset. After that, we will load the two R packages “corrplot” and “glmnet.” By using the cor() function, we will create a correlation object “corrlate” and visualize the correlation coefficient. The predictors and outcome variables in the training and validation sets will be encoded into matrices, the predictors will be stored in X vectors, and the outcome variables in Y vectors. A LASSO regression will be performed when alpha is set to one. The program will then be run. When the parameter lambda is greater, the estimated parameters will also be compressed to a smaller degree. As lambda reaches a certain value, some variables that are not important to the model will be compressed to zero, indicating that these variables will be eliminated. Thus, the lambda corresponding to the optimal result, the influencing factors of preliminary screening, and the regression coefficient will be obtained.

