#### Internal validation and assessment of model performance

Internal validation will be conducted using the 20% validation set samples and will utilize a cross-validation method based on 10 folds. Then, the result of LASSO cross-validation will be obtained, and the lambda when it is one standard error away from the mean square error will be considered optimal (at this time, the mean square error is small, and the number of independent variables is also small). For that lambda case, we will examine the regression coefficients and exclude variables with a regression coefficient of zero. Those variables with regression coefficients other than zero are selected, thereby identifying the influencing factors that are significantly associated with depression in PCOS adolescents. After screening the variables, a multivariate linear model will be constructed.

The prediction accuracy of the model will be reflected by discrimination and calibration. In this study, the C-statistic is used to measure discrimination, followed by a calibration plot to measure the accuracy of the absolute risk predictions of the warning model. An evaluation of the fit will be performed by drawing a scatter plot.

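### External validation is defined to include refitting the model in the September–December cohort, and the plan never says performance is computed from the fixed January–August model

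*Protocol article*

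**What the plan says.** The Abstract and Patient recruitment sections keep the later patients apart from development: "data collected between September 2022 and December 2022 will be used for external validation", and again "Data collected from September 2022 to December 2022 as an external validation cohort". The January–August data are used for development and internal validation, and "it will be divided into 80% training data and 20% validation data".

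The External validation section gives the purpose: "External validation will be conducted using temporal validation with data collected from September 2022 to December 2022, to ensure model portability and generalizability". Its next sentence spells out what this means in practice: "model risk scores will be calculated rigorously and the model will be refitted in the validation cohort". No performance measure is named there. The measures appear under Internal validation and assessment of model performance, where "the C-statistic is used to measure discrimination, followed by a calibration plot to measure the accuracy of the absolute risk predictions". Objective (ii) is to "Validate the accuracy and validity of the model and to assess the clinical utility of the model".

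No section says that the January–August equation is held fixed when it is taken to the September–December cohort. The Discussion names the limits of single-centre temporal validation but does not mention the refit.

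**The concern.** External validation asks whether an equation already estimated predicts well in patients who played no part in estimating it. Once the coefficients are re-estimated in those patients, the result is a different equation judged on its own fitting data. That answers another question, and the answer is favourably biased.

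The sentence presents the refit as part of the validation, not as a later updating step. If the C-statistic and calibration plot are taken from the refitted model, a development model that fails in the later period could still be reported as validated. The September–December cohort is the only external evidence in the plan. The nomogram for clinic use is to be drawn up once the model is defined, so a refit also leaves open which set of coefficients it would carry.

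**Working it through.** **The plan's own figure.** The only computed figure is in Sample size and calculation: "a minimum of 369 participants is needed to aim for an estimation error of no more than 0.05 around the actual value of 0.4". Check: n = (1.96/0.05)² × 0.4 × 0.6 = 368.79, rounded up to 369. It reproduces, and this point does not depend on it.

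**What follows from algebra alone.** Take an unpenalised logistic model refitted in the external cohort, with fitted risks p_i and linear predictor lp_i = a + Σ_j b_j x_ij. Maximum likelihood solves

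- Σ_i (y_i − p_i) = 0, so mean predicted risk equals observed risk and calibration-in-the-large is 0;
- Σ_i x_ij (y_i − p_i) = 0 for every predictor j, hence Σ_i lp_i (y_i − p_i) = 0.

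These are the estimating equations of the calibration model logit(p) = α + β·lp, solved at α = 0 and β = 1. The refitted model therefore has a slope of 1 in that cohort whatever the data. The same holds for least squares with an intercept, which matters because the plan speaks of a multivariate linear model after LASSO screening.

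**Inputs for an illustration of size.**

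- From the documents: 800 PCOS patients over 12 months, the 80/20 split and an outcome proportion of 0.4.
- Assuming even accrual: development 800 × 8/12 = 533; training 0.8 × 533 ≈ 427; external 800 × 4/12 = 267.
- The Participants section's 80–100 patients a month gives 4 × 80 = 320 to 4 × 100 = 400 external patients, so 400 was run as well.
- Assumed, not in the documents: logistic form; 10 or 20 retained, independent, equally strong predictors; 400 runs per setting.

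**Later cohort drawn from the same population (means over runs).**

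| Predictors | External n | Frozen: C, slope | Refitted: C, slope | Gain in C |
|---|---|---|---|---|
| 10 | 267 | 0.709, 0.87 | 0.744, 1.00 | 0.035 |
| 10 | 400 | 0.707, 0.86 | 0.735, 1.00 | 0.028 |
| 20 | 267 | 0.693, 0.72 | 0.767, 1.00 | 0.074 |
| 20 | 400 | 0.695, 0.73 | 0.752, 1.00 | 0.057 |

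**Later cohort in which the developed model fails or shifts (10 predictors, n = 267).**

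| Scenario | Frozen model | Refitted model |
|---|---|---|
| Half the effects reversed | C 0.50, slope 0.00 | C 0.74, slope 1.00 |
| Baseline risk lower by 1 logit | over-predicts by 0.18 on average | mean error 0.00 |
| No predictor has any effect | C 0.50 | C 0.61 (0.66 with 20 predictors) |

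**A variant with selection.** With 45 candidate parameters, 8 of them truly predictive (also assumed), 427 training and 267 external patients, and 135 runs, the frozen model gave C 0.703 and slope 0.751. Refitting the selected variables gave an apparent C of 0.742 and slope of 1.000. In 20,000 new patients the refitted model's C was 0.699, so its apparent value was optimistic by 0.742 − 0.699 = 0.043.

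**Range.** Varying predictor count, effect size, penalty and external n further gives frozen slopes of about 0.55–0.9 and gains in C of about 0.02–0.10.

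**If the LASSO itself is refitted.** With two assumed fixed penalties the apparent slope was about 2.0–2.8, because the coefficients are shrunk. Slope 1 is thus a property of the unpenalised refit only. The penalised figure is no more a validation, since it too comes from the fitting data.

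**The case against.** The strongest reply is that the sentence has two halves. Calculating the model's risk scores in a later cohort would naturally mean applying the developed equation, and that is genuine validation if those scores are then evaluated. The Study design section also commits to expert guidance on development and validation and to TRIPOD reporting, and the stated aim is portability. This stands in part. A reader might infer that the plan replaces scoring with refitting, and the text does not support going that far. But it does not say that coefficients are held fixed, nor that the C-statistic and calibration come from the scores rather than from the refit. On the charitable reading the sentence still counts a refit as validation and needs correcting.

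A reader might also infer that any refit must show a slope of exactly 1 and near-perfect calibration. That holds for calibration-in-the-large and the linear slope of an unpenalised refit. It does not hold for a refitted LASSO, and a calibration plot of a refitted model can still reveal non-linear misfit. The section does not say which model is refitted.

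A third inference would be that objective (ii) cannot be met at all. The objective is not tied to the later cohort, and the held-out 20% of the January–August data is also planned for validation. Only the external, temporal part is at risk.

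The simulation rests on assumed predictor counts and effect sizes. Its range is illustrative, and no single figure from it should be quoted as the plan's error.

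**Conclusion.** The concern holds for the stated procedure. The External validation section makes a refit part of the validation and leaves unsaid which predictions are evaluated. Performance taken from the refitted model would be apparent performance of a new model and could not detect failure of the developed one. That conclusion follows from the wording and from the algebra of unpenalised fitting. The simulation adds only a sense of scale: a frozen slope of roughly 0.55–0.9 shown as 1.00, and C inflated by roughly 0.02–0.10, for an external n of 267–400 under assumed effects.

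Confidence is high that the sentence is wrong as written. It is moderate on what the analysts would actually do, because the risk-score half allows a sound analysis without specifying it. A missing analysis plan does not remove the problem, since the article states the rule itself.

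**What to change.** Replace the sentence that calls for refitting with:

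> The intercept and coefficients of the final January–August model are frozen and applied unchanged to the September–December cohort; the C-statistic, calibration intercept, calibration slope and calibration plot are computed from those predictions with 95% CIs. Any refit or recalibration is reported afterwards, separately, as model updating and not as validation.

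The cost is one sentence of wording, with no new data. The downside is that reported performance may look less favourable than a refit would make it.

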### Data storage and management

Data will be entered and stored through a third-party electronic platform, and all documents and data will be password-protected on a network within the platform, accessible only to researchers. Data will be exported in Excel format for further analysis when processed.

## Discussion

This research protocol aims to construct and validate a warning model for depression in adolescents with PCOS. It will answer three questions: what factors influence depression risk in adolescents with PCOS; what role do various types of depression risk factors play in the development of depression in adolescents with PCOS; and how interpretable and accurate is the LASSO-based warning system.

There are many factors associated with depression in adolescents with PCOS. For the first time, a depression warning model will be constructed that takes into account not only general factors like individual susceptibility factors, biological factors, and psychosocial environmental factors of depression in adolescence, but also the pathological factors, illness perception factors, diagnosis and treatment factors, and symptom-related factors of PCOS. This study will precisely and early identify depression at-risk groups for PCOS in adolescence by including the influencing factors of several dimensions of depression into the model and leveraging LASSO's ability to automatically screen variables and boost model interpretability.

So far, it has been difficult to identify adolescents at high-risk of depression, which has a severe impact on adolescent mental health. In this study, the research population consists of adolescents with PCOS, who have a significantly greater prevalence of depression and more complicated impacts than general adolescent girls, an important representative sample. Through this study, we hope to remove the bottleneck of identifying adolescents at risk of depression. The success of this study can not only identify the high-risk groups of depression in adolescents with PCOS, but also demonstrate the risk factors and key links associated with depression in adolescents with PCOS. At the same time, it can be extended and applied to the management of high-risk groups of depression throughout adolescent girls, thereby contributing to reducing the prevalence of depression in adolescent girls and implementing comprehensive and effective prevention measures.

The study is a retrospective cohort study, and the questionnaire will be partially completed by patients' recollection of recent events, which may be subject to a degree of recall bias. In prospective cohort studies, depression outcomes and factors contributing to depression can be longitudinally tracked over a period of time of high-risk groups with PCOS in adolescence, which can help to make models more robust and representative. Data for this study will be collected at one hospital, so it will be a single-center study. It is proposed that future studies should collect data from multiple hospitals simultaneously to increase sample size and persuasiveness. In this study, participants will be selected in accordance with the diagnostic criteria prescribed in the “Chinese guidelines for diagnosis and treatment of polycystic ovary syndrome.” Due to the inconsistency in diagnostic criteria among different ethnic groups, the generalizability of this study is limited to some degree. It is recommended that metformin and oral contraceptives be used to treat PCOS in adolescence, in accordance with international evidence-based guidelines (4). It has been reported, that oral contraceptives may increase participants' risk of depression (24), whereas metformin can help to alleviate depression (52). Hence, confounding effects may occur if participants take metformin and oral contraceptives concurrently. As part of our investigation, we will assess the medication status of the participants. However, we will not be able to eliminate the possibility that there may be a confounding effect. The model was externally validated using temporal validation, as the data source is the same as the model development cohort, which may be less transferable and generalizable than geographical validation (which validates the model against data from other centers or even other countries).

## Ethics statement

The studies involving human participants were reviewed and approved by the Ethics Committee of ZunyiMedical University: Zunhe Lun Review [2021] 1-093. Written informed consent to participate in this study will be provided by the participant's legal guardian/next of kin. Written informed consent will be obtained from the individuals and minor's legal guardian/next of kin, for the publication of any potentially identifiable images or data included in this article.

